### Planned Recruitment Rate

There are approximately 18,500 live births per year in Calgary [48]. Recruitment for the All Our Babies Cohort Study began September 2009 and is targeted for completion late 2010. The recruitment rate has averaged 36 participants/week through the community laboratory services and represents approximately 10% of births in Calgary during this period.

### Study Compliance

Strategies used to maintain participant involvement include reminder phone calls for outstanding questionnaires and providing incentives including public library gift certificates and grocery gift certificates for completed questionnaires. Mailing the questionnaires and providing postage paid envelopes has minimized time and costs to participants.

The All Our Babies Cohort Study participants are provided with two options for blood collections. Women may schedule an appointment through the research team at a central community laboratory clinic within Calgary. For participants unable or unwilling to travel to the laboratory clinic, the research team will send a certified mobile phlebotomist to the women's home or other neutral location of her choice for the blood collections. In appreciation for their time and commitment to the study, women are provided with department store gift certificates at the time of their blood collection.

Umbilical cord blood samples collected at the time of birth at local hospital births are sent to a single transfusion medicine laboratory location. The research team is notified of delivery and obtains these specimens after all clinical testing is completed. Women and their health care providers therefore do not need to do anything at the time of delivery for the study. Study team members need not be present at delivery units.

### Anticipated Rate of Loss To Follow-Up

The All Our Babies Cohort Study anticipates retaining 85% of women after completion of the first questionnaire and excluding miscarriages. Based on women's consent to participate in follow-up studies of 97% and with dedicated retention strategies, it is anticipated that no more than 10% of study participants will be lost to follow-up into the preschool years.

### Proposed Type and Frequency of Analysis

#### Transcriptomic Analysis

RNA will be extracted from samples collected from identified cases (spontaneous preterm births with or without PPROM) and controls (term deliveries). Cases and controls will be 'loosely matched' such that each group has a similar distribution of maternal ages, prepregnancy body mass indexes and smoking status. Extracted RNA will be aliquoted into three tubes - one for Agilent RNA quality assessment, one for the transcriptomic microarray, and one for validation of microarray findings by real time polymerase chain reaction. Samples will be run on Affymetrix microarrays in two batches of 40 cases and 40 controls. All statistical analyses will be conducted on the full dataset generated from the microarrays.

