The pathophysiology of preterm birth is complex due to multi-factorial causes and its heterogeneous nature. Preterm birth is often categorized as (1) iatrogenic when delivery is a consequence of medical intervention (30-35%); (2) spontaneous when it occurs after spontaneous labour with intact membranes (40-45%); or (3) the result of preterm premature rupture of the membranes (PPROM) (25-30%) [3]. While gestational diabetes, preeclampsia and intrauterine growth restriction have all been associated with iatrogenic preterm birth, the underlying causes of spontaneous preterm birth are less clear. Reported risk factors are widespread and diverse, supporting the hypothesis of gene-gene and gene-environment interactions in the pathophysiology of spontaneous preterm birth. Highly associated risk factors include a previous preterm birth or a relative with preterm birth [10] or a black racial background [11], suggesting genetic causes. Other demographic factors such as low socioeconomic status [12] and maternal stress [13] have shown an association, indicating that the environment contributes to the etiology of spontaneous preterm birth.

Evidence for a causal role of infection and inflammation in preterm birth has been reviewed in detail [14]. Both interleukin (IL)-1β and tumor necrosis factor (TNF)α are cytokines produced by the intrauterine tissues in response to bacterial infections [15,16] which stimulate prostaglandin synthesis [17] and increase uterine contractility. Several groups have investigated the relationship between a single nucleotide polymorphism (SNP) located in the promoter of the TNFα gene (G-308>A) (referred to as the TNF-2 allele) and preterm birth, but inconsistent results have been reported [18-21]. A recent meta-analysis of seven studies [22] found no association between preterm parturition and the TNF-2 allele. Similarly, studies examining polymorphisms in IL-1β and IL-6 as well as other variants have also produced inconsistent results [19,23,24].

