### Inclusion Criteria

Inclusion criteria for the All Our Babies Cohort Study are designed to ensure women most at risk of preterm birth are captured in the cohort.

1. Women <17 weeks 6 days gestation at time of recruitment

2. Women receiving prenatal care in Calgary

3. Women able to understand written and spoken English

4. Age 18 years or older at time of enrollment

5. One of the following pregnancy histories:

a. Nulliparous or primiparous OR

b. A personal or familial history of preterm birth

6. Singleton pregnancy

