### Sample Size

Sample size calculations for the All Our Babies Cohort Study required complex considerations as maternal blood samples are destined for microarray analyses. Several power calculations for microarray methodologies exist, consequently sample size was determined and compared with two power calculation approaches. The first approach uses a two-class comparison model with a significance level of 0.001, a power of 0.95, one technical replicate per sample and estimated values of τ^2 ^+ 2 γ^2 ^= 0.25 and τ^2^/γ^2 ^= 4 (where τ^2 ^is the biological variance within class of log ratios and γ^2 ^is the technical variance of log ratios); the minimum sample size to identify a two-fold change in gene expression between classes is thus 25 patients in each study group [42,43]. An alternate approach is to consider the sample size required to detect a two-fold change in the expression levels of the 90% and 75% least-variable genes for a given set of false positive rates and power [42]; using previously published human tissue microarray data [43] and setting the false positive rates at 0.001 and a power of 0.9, this approach gave a minimum of 18 and 13 patients in each group to detect a two-fold change in expression levels for the 90% and 75% least-variable genes, respectively. Microarrays will be performed on RNA samples collected from 80 cases of spontaneous preterm birth and 80 matched controls (160 biological replicates) from samples collected at two time points (18-22 weeks and 28-32 weeks): a total of 320 microarrays. This sample size will allow prediction of:

1) idiopathic PTB (n~40), including

a) idiopathic PTB prior to 32 weeks gestation (n~13); and

b) idiopathic PTB between 32 and 37 weeks gestation (n~27);

2) PPROM and PTB (n~40), including

a) PPROM and PTB prior to 32 weeks gestation (n~13);

b) PPROM and PTB between 32 and 37 weeks gestation (n~27);

3) spontaneous PTB (n~80), including

a) spontaneous PTB prior to 32 weeks (n~25); and

b) spontaneous PTB between 32 and 37 weeks gestation (n~55).

Therefore, with a preterm birth rate of 9.1% in Alberta, an anticipated miscarriage rate of 5% and an anticipated loss to follow-up rate of 15% based on experience with other Alberta based cohorts [44], 2200 women will be enrolled in the All Our Babies Cohort Study. This should ensure 1800 women complete the study, of which approximately 180 will have preterm birth outcomes and approximately 120 of these will be spontaneous with or without PPROM.

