### Significance of The Study

The rate of preterm birth is on the rise in the developed world. Alberta has the highest provincial preterm birth rate in Canada, the causes of which remain unexplained. The All Our Babies Cohort Study is strategically situated to examine the environmental, medical and genetic factors impacting preterm birth in Alberta and seeks to exploit their predictive properties for future clinical screening of all pregnant women. Should gene expression patterns predictive of spontaneous preterm birth be elucidated or gene-environment interactions protective against or synergistic for a spontaneous preterm birth outcome be discovered, the detailed phenotypic information will inform validation endeavors. This could potentially expedite the journey from basic science discovery to clinical utility, a translation process which to date has had limited success in the applications of 'omics technologies in maternal-fetal newborn health. In addition, this study will improve our understanding of how social support and social services impact spontaneous preterm birth in Calgary.

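### An array signature may partly reflect parity, preterm history or ethnicity, because eligibility ties higher parity to preterm history and none of the three is balanced or set as a baseline to beat

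*Protocol article*

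**What the plan says.** **Inclusion Criteria.** The criteria are "designed to ensure women most at risk of preterm birth are captured in the cohort". Criterion 5 has two routes. Route a is "Nulliparous or primiparous OR" and needs no history. Route b is "A personal or familial history of preterm birth". Route b is the only way in for a woman with two or more earlier births.

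**Background.** The article states: "Highly associated risk factors include a previous preterm birth or a relative with preterm birth", and adds "or a black racial background".

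**Sample Size and Transcriptomic Analysis.** Arrays are run on "80 cases of spontaneous preterm birth and 80 matched controls" at two time points. The matching is described as loose, so that "each group has a similar distribution of maternal ages, prepregnancy body mass indexes and smoking status". No other balancing factor is named.

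**Statistical Analysis.** Transcriptomic, record and questionnaire data are first analysed univariately. If a predictive signature is found and validated, it is then combined with questionnaire and record data to explore gene-environment interactions.

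**Significance of The Study.** The study hopes to use the "predictive properties for future clinical screening of all pregnant women".

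**The concern.** By rule, every enrolled woman with two or more earlier births has a personal or familial preterm history. If history raises risk, as the Background says, higher parity will be more common among cases than controls even if parity has no effect on risk. Cases should also be enriched for history itself and for any ethnic group at higher risk. The three balancing factors do not address this directly, and the described analysis contains no step that separates expression linked to these traits from expression that predicts beyond them.

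Two things are at stake:

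- **Added value.** A transcript score that tracks history or ancestry separates cases from controls but may tell a clinician little that a short interview does not.
- **Transport.** Part of the parity-case link is created by who was let in. A screen for all pregnant women would also be applied to women with two or more earlier births and no preterm history, whom this study excludes.

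**Working it through.** The plan states no figure on this point, so there is none to reproduce. The structural part follows from the text. The arithmetic shows how large the effect could be, and every input marked *assumed* is absent from the documents.

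**1. Imbalance in preterm history.** Let p be the share of the cohort with a history and RR its relative risk (*assumed* 10-20% and 2-3). The share of cases with a history is p × RR / (p × RR + 1 − p). The control share is taken as p, since most women deliver at term. There are 80 women per group (Sample Size).

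| p | RR | Share of cases | Cases of 80 | Controls of 80 | Imbalance (points) |
|---|---|---|---|---|---|
| 10% | 2 | 0.20/1.10 = 18% | 15 | 8 | 8 |
| 10% | 3 | 0.30/1.20 = 25% | 20 | 8 | 15 |
| 20% | 2 | 0.40/1.20 = 33% | 27 | 16 | 13 |
| 20% | 3 | 0.60/1.40 = 43% | 34 | 16 | 23 |

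**2. Parity link produced by eligibility alone.** Give parity no effect on risk. Let m be the share of the cohort with two or more earlier births (*assumed* 5-20%; all history-positive by criterion 5). Let h be the share with a history among the other women (*assumed* 10%), and RR the relative risk for history (*assumed* 1.5-4). Spontaneous preterm birth is *assumed* at 6%, close to the 120 of 1800 (6.7%) in Sample Size.

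- History share: H = m + (1 − m)h
- Risk without history: b = 0.06 / (1 − H + H × RR)
- Higher-parity share of cases: m × RR / (1 − H + H × RR)
- Higher-parity share of controls: m(1 − RR × b) / 0.94

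With m = 10% and RR = 2: H = 0.19 and b = 0.06/1.19 = 0.0504. The case share is 0.20/1.19 = 16.8% and the control share is 0.10 × (1 − 0.1008)/0.94 = 9.6%. The odds ratio is (0.168/0.832)/(0.096/0.904), about 1.9. Over the whole assumed range it runs from about 1.5 to 3.5, although parity was given no effect.

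**3. Chance that a gene marking only the trait reaches p<0.001.** Let the gene differ by d on the log2 scale between women with and without the trait and have no other link to preterm birth. Take a within-class variance of 0.25 (the value of the variance sum in Sample Size) and a two-sided level of 0.001 (sidedness is not stated). With trait shares p1 in cases and p0 in controls:

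SE = √{[2 × 0.25 + d²(p0(1 − p0) + p1(1 − p1))]/80}

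P = Φ(d(p1 − p0)/SE − 3.29)

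- Two-fold gene (d = 1), smallest imbalance in step 1: SE = √(0.739/80) = 0.096. The ratio is 0.082/0.096 = 0.85, so P = Φ(−2.44), about 1%.
- Two-fold gene, largest imbalance: SE = √(0.905/80) = 0.106. The ratio is 0.229/0.106 = 2.15, so P = Φ(−1.14), about 13%.
- Four-fold gene (d = 2), with 15% of controls carrying the trait: about 3% at a 10-point imbalance and 24% at 20 points.

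The chance per gene is small at low imbalance and rises with the imbalance. It applies separately to each gene linked to the trait, and the documents do not say how many such genes exist.

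**The case against.** The strongest reply has four parts.

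*A condensed article leaves adjustment to the analysis plan.* The plan is not shown and may adjust; univariate analysis is only called the first step. That stands, so the point is not that adjustment is missing. It is that the article fixes a matching set, an order of analysis and a target population that fit together badly. Aim (c), outcome (c) and the comparison of participants with the Alberta and Canadian populations touch the subject. None of them adjusts for these traits or tests what a signature adds to them.

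*Leaving history and ethnicity unmatched is defensible.* The Background reads these factors as pointing to genetic causes, and aim (a) is about genetic components. Matching on them could remove signal that the study seeks. This stands, and the fix leaves the matching alone.

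*A history-linked marker is not false.* This also stands: it would still predict in this cohort. A reader might infer that such a signature would be spurious, but the documents do not support that. What remains open is its added value and, for the parity-linked part, its transport.

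*The screening statement is an aspiration.* It speaks of future screening, and the same section mentions validation. That softens the statement, but it still names a population wider than the one enrolled.

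**Conclusion.** The point holds as a risk to interpretation, not as a demonstrated bias. It is certain from the text that higher parity implies a personal or familial preterm history in this cohort, and that the stated balancing omits parity, history and ethnicity. How much this distorts a signature depends on an imbalance the documents do not give. Under the assumed ranges, history differs by about 8-23 percentage points between cases and controls, and a two-fold history-linked gene has about a 1-13% chance of passing p<0.001.

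Two stronger readings are tempting and should be resisted:

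- A reader might infer that any expression difference linked to parity or ancestry will show up as a case-control difference. The probabilities above do not support that.
- A reader might infer that eligibility also distorts ethnicity. Criterion 5 does not select on it; ethnicity enters only as an unmatched risk factor, and the documents give no basis for sizing its effect.

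The change is worth making because it is cheap and alters what the study can conclude.

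**What to change.** 1. Leave the matching as it is.
2. Fit a baseline model with preterm history, parity and ethnicity, and report each signature's added discrimination over it. Eligibility screening and the questionnaires already cover pregnancy history and demographics. Confirm that familial history and ethnicity are recorded for every woman in the array set, including those admitted as nulliparous or primiparous.
3. As a sensitivity analysis, repeat the comparison in nulliparous and primiparous women without a personal or familial preterm history. Under the assumed ranges this keeps roughly 46-65 cases (80 − 34 to 80 − 15) and 64-72 controls (80 − 16 to 80 − 8).
4. In Significance of The Study, limit the screening statement to the enrolled population (nulliparous, primiparous or history-positive women meeting the other criteria), pending validation in unselected women.

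The cost is analysis wording, with no new samples or arrays. The downsides are a smaller reported predictive gain, a less precise restricted analysis and a narrower claim.

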#### Statistical Analysis

Transcriptomic data, medical record data and self-report questionnaire data will first be analyzed univariately. Participant characteristics will be assessed and compared to the pregnant and parenting population in the province of Alberta and nationwide across Canada. Should transcriptomic signatures predictive of preterm delivery phenotypes be elucidated from the microarray analyses and validation, gene-environment interactions will be explored by integrating the transcriptomic data with the questionnaire and medical record datasets using appropriate statistical analytical techniques.

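### The only validation named for the expression signatures is RT-PCR on the same women's RNA, which cannot show that a signature predicts, yet the decision to go on to aim (c) rests on it

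*Protocol article*

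**What the plan says.** Prediction is the intended product. Proposed Outcome Measures looks for expression patterns that predict preterm delivery, and Sample Size, after calculations for two-fold changes in single genes, introduces a list of phenotypes with "This sample size will allow prediction of". Two of the listed strata have about 13 cases.

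On the data, Transcriptomic Analysis says "Samples will be run on Affymetrix microarrays in two batches of 40 cases and 40 controls", and the next sentence is "All statistical analyses will be conducted on the full dataset generated from the microarrays".

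On validation, the same section says "Extracted RNA will be aliquoted into three tubes": one for RNA quality, one for the array, and "one for validation of microarray findings by real time polymerase chain reaction". No other validation material is named there.

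On what follows, Statistical Analysis begins with a univariate analysis of the transcriptomic data. It then makes the gene-environment work conditional: "Should transcriptomic signatures predictive of preterm delivery phenotypes be elucidated from the microarray analyses and validation". Significance of The Study mentions later validation efforts, without a sample or a plan.

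**The concern.** A signature picked from thousands of transcripts always separates the women from whom it was picked. Whether it predicts can be judged only in women who played no part in choosing the genes or fitting the score.

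RT-PCR on a third aliquot does not provide such women. It re-measures the same biological material, so a chance difference between these cases and these controls appears again. It can expose an array artefact but not a chance finding.

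At stake is the decision to call a signature predictive and to move to aim (c). The article also looks ahead to clinical screening of all pregnant women, where an inflated accuracy figure would do most harm. The per-gene calculation does not repair this, because power to see a two-fold change in one gene says nothing about the accuracy of a multi-gene score.

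**Working it through.** **1. The plan's own figure.** Women on arrays: 80 + 80 = 160. Two time points: 160 × 2 = 320, which matches "a total of 320 microarrays". The batches agree: 2 × (40 + 40) = 160 women. The article states no predictive accuracy, so there is none to reproduce.

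**2. What RT-PCR shares with the array.** Write an array value as biology plus technical error, and the RT-PCR value as the same biology plus new error. Sample Size gives a biological-to-technical variance ratio of 4. If that ratio also holds for RT-PCR (an assumption), the two measurements correlate at 4 / (4 + 1) = 0.8. Most of any chance pattern carries over.

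**3. Null simulation.** There is no true case-control difference in any gene.

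- From the document: group sizes 80, 40 and 13; the 4:1 variance ratio; the batch split.
- Assumed: 2,000, 5,000 or 20,000 independent normal genes; k = 10, 20 or 50 genes kept; controls equal in number to cases.
- Selection: t = d / √[v(1/n₁ + 1/n₀)], where d is the mean difference and v the pooled variance; keep the k largest |t|.
- Score: Σ (d/v)(x − midpoint) over the kept genes.
- AUC = [R₁ − n₁(n₁ + 1)/2] / (n₁n₀), where R₁ is the rank sum of the cases.
- 20 runs per row (40 for 2,000 and 5,000 genes); 10-fold cross-validation (CV), 5-fold at 13 per group.

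Mean AUC:

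| Per group | Genes | k | Same arrays | Same RNA re-measured | CV, genes chosen beforehand on all arrays | CV, genes chosen inside folds | Batch 1 to batch 2 | New women |
|---|---|---|---|---|---|---|---|---|
| 80 | 2,000 | 10 | 0.869 | 0.818 | 0.840 | 0.488 | 0.501 | 0.522 |
| 80 | 5,000 | 10 | 0.889 | 0.833 | 0.866 | 0.502 | 0.511 | 0.490 |
| 80 | 20,000 | 10 | 0.915 | 0.860 | 0.896 | 0.493 | 0.508 | 0.508 |
| 80 | 20,000 | 20 | 0.964 | 0.927 | 0.948 | 0.469 | 0.497 | 0.495 |
| 80 | 20,000 | 50 | 0.997 | 0.981 | 0.992 | 0.498 | 0.500 | 0.502 |
| 40 | 20,000 | 10 | 0.975 | 0.945 | 0.964 | 0.531 | – | 0.497 |
| 13 | 20,000 | 10 | 1.000 | 0.996 | 1.000 | 0.460 | – | 0.499 |

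**4. Reading the table.**

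- Re-measuring the same RNA lowers the AUC only slightly and leaves it far above the true 0.50.
- Cross-validation does not help if the genes were chosen beforehand on all arrays. This matters because the univariate step comes first.
- Selection inside the folds, or a batch that took no part in selection, returns the result to chance. Both use only arrays already planned.

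**5. Precision of an out-of-sample figure.** Null SE of AUC = √[(n₁ + n₀ + 1) / (12 n₁n₀)]. For one test batch of 40 v 40: √(81 / 19,200) = 0.065. In a stratum of 13 cases, training on one batch leaves 13 / 2, or 6 to 7 cases, below each of the per-group minima in Sample Size (13, 18 and 25).

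**The case against.** The sentence on the full dataset directly follows the one on the two batches. Its natural meaning may be only that the batches are pooled and the first is not analysed alone. Cross-validation with gene selection inside the folds also uses the full dataset. The article names no classifier, selection rule or accuracy measure; such detail commonly sits in an analysis plan that is not shown, so its absence is not a fault. Passing the condition in Statistical Analysis leads only to exploratory work, and later validation is anticipated. The simulated procedure is an illustration, not the study's stated method.

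All of this stands, and it limits the point. A reader might infer that the study will report in-sample accuracy, or that its reported accuracy will be badly optimistic. The document supports neither: it commits to no accuracy estimate and does not exclude honest resampling.

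What the objection leaves untouched is what the article does state. It calls a same-RNA check validation, names no other, and puts it into the condition for declaring a predictive signature. No unseen analysis plan can turn that check into a test of prediction.

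**Conclusion.** The point holds in conditional form. The named validation cannot tell a predictive signature from a chance one, and the full-dataset sentence, as worded, leaves open whether anything else will. If genes are selected and judged on the same arrays, null data at 80 v 80 give a mean AUC of 0.87 to 0.997, and 0.82 to 0.98 on re-measurement of the same RNA, against 0.49 to 0.52 in new women. At 13 v 13 the first two figures are 1.00 and 0.996.

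The sizes rest on an assumed gene count, an assumed number of genes kept, independent genes, and the array variance ratio carried over to RT-PCR. They move with these choices; the direction does not change over the range tried. They show what the named check would let through, not what this study will find.

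**What to change.** In Transcriptomic Analysis and Statistical Analysis, state that:

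- full dataset means that both batches are used, while predictive performance is estimated out of sample;
- all gene selection, including any univariate screen, and all fitting take place inside the training data, either by nested cross-validation or by training on one batch and testing on the other;
- both samples of a woman stay on the same side of every split;
- the condition for moving to aim (c) rests on the out-of-sample AUC, sensitivity and specificity, with intervals;
- RT-PCR is technical confirmation of the array measurement.

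In Sample Size, describe results in the strata of about 13 cases as exploratory, in place of "This sample size will allow prediction of" for those strata.

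No further women or arrays are needed. The cost is a wider interval (null SE of AUC about 0.065 when one batch of 40 v 40 is the test set) and a less favourable accuracy figure. The batch split also halves the training data, so nested cross-validation is the more workable choice in the smaller strata.
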